# 1. TRIAL SUMMARY

| **TITLE** | A randomised trial to determine the effectiveness of the Preparing For Life programme which aims to improve the school readiness skills of socioeconomically disadvantaged children in Dublin, Ireland |
| --- | --- |
| **OBJECTIVES** | **Primary objective**  To test the effectiveness of the Preparing for Life (PFL) programme at improving the school readiness skills and life outcomes of socioeconomically disadvantaged children.  **Secondary objective**  To test the effectiveness of the Preparing for Life (PFL) programme at improving parental skills and the quality of the home environment. |
| **DESIGN** | Randomised controlled trial |
| **SAMPLE SIZE** | 300 (100 in randomised high treatment group; 100 in randomised low treatment group and 100 in external comparison group) |
| **STUDY POPULATION** | Pregnant women residing in the PFL catchment area |
| **ELIGIBILITY CRITERIA** | **Inclusion criteria**   1. Women (age 16+) pregnant between 2008 and 2010 2. Residing in the PFL catchment area 3. Willing to be assigned to either of the study intervention groups 4. Written informed parental/carer consent   **Exclusion criteria**   1. Under the age of 16 2. Not pregnant 3. Not residing in the PFL catchment area 4. No written consent provided. |
| **TREATMENT** | **5 year home visiting mentoring programme & group Triple P parenting programme** |

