# 4. OBJECTIVES

- To undertake a randomised controlled trial to evaluate whether, compared to the low treatment group, the PFL home visiting programme and group Triple P leads to improved school readiness skills among 4/5 year old children who are socioeconomically vulnerable.

- To use a quasi-experimental design to evaluate whether, compared to the external comparison group, the low treatment supports leads to improved school readiness skills among 4/5 year old children who are socioeconomically vulnerable.

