**7. Trial Intervention**

**7.1 High treatment intervention**

*PFL* is a community-based home visiting programme (HVP) which aims to improve children’s school readiness skills by intervening during pregnancy and working with families until the children start school at age 4/5 years. The high treatment group will receive twice monthly home visits, lasting approximately one hour, delivered by mentors from a cross-section of professional backgrounds such as psychologists and family support specialists. Mentors will receive extensive training prior to programme implementation and monthly supervision thereafter to ensure fidelity to the programme model. Each family will be assigned the same mentor over the course of the intervention where possible. The mentors will use role modelling, demonstration, coaching, discussion, encouragement, and feedback to deliver the intervention, as well as direct interactions with the child in the presence of the parent. The aim of the visits are to support and educate the parents on key child rearing issues including the identification of developmental milestones and appropriate parenting practices that promote the children’s health, and cognitive and non-cognitive development. Each visit will be guided by a set of *PFL* ‘Tip Sheets’ which are based on pre-existing governmental and local non-governmental organisations’ recommendations, and present best-practice information on pregnancy, parenting, and child health and development. There are three sets of age-specific Tip Sheets - pre-birth-12 months, 1-2 years, and 2-4 years. There are approximately 150 *PFL* Tip Sheets as part of the programme’s curriculum. The mentors will be able to choose when to deliver the Tip Sheets within these specific time periods based on the age of the child and the needs of the family. The Tip Sheets will be given to the participants at the end of each visit to keep as an on-going resource.

The high treatment group will also be invited to participate in an additional parenting course (Triple P Positive Parenting Program; Sanders et al., 2003) when their children are between 2 and 3 years old i.e., after they have completed the 24-month assessment. Triple P promotes healthy parenting practices and positive parent-child attachment. The intervention will involve the delivery of Group Triple P which consists of 5 two-hour group discussion sessions and 3 individual phone calls facilitated by the mentors.

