**7.2 Low treatment intervention**

Both the high and low treatment groups will receive some common supports including developmental materials and book packs. The developmental packs will consist of materials such as a baby gym, food utensils, safety items and an assortment of developmental toys. Both groups will also be encouraged by letter and text message to attend public health workshops on stress management and healthy eating which are already taking place in the community. The low treatment group will also have access to a support worker who can help them avail of community services if needed, while this function will be provided by the mentors for the high treatment group.

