**7.3 External comparison group intervention**

The external comparison group, which will be selected from a socio-demographically similar community, will receive care-as-usual only. Care as usual, which is available to all pregnant women and infants in Ireland, is as follows: Expectant mothers are provided with an initial family doctor (G.P.)/obstetrician appointment at 12 weeks and a further 5 examinations for first time mothers and 6 for subsequent pregnancies. Antenatal classes are provided by local public maternity hospitals free of charge. Following birth, a G.P. examination is carried out for the baby at 2 weeks and mother and baby at 6 weeks. The mother is entitled to free in-patient, out-patient and accident and emergency/casualty services in public hospitals in respect of the pregnancy and the birth and is not liable for any hospital charges. In addition, checks by a public health nurse are generally carried out in the home in the weeks after birth and when the infant is 9, 18, and 24 months, but they are not mandatory. A schedule of immunizations in provided free of charge at birth, 2, 4, 6, 12, and 13 months

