**12.2 Data Analysis**

The primary analysis will be by intention to treat (ITT). All statistical analysis will involve comparing both treatment group A (high dosage) to treatment group B (low dosage), and groups (A+B) to control group C (external comparison group). A simple analysis of the randomised experiment will tell us if the PFL programme had a causal effect. Then, by modelling the possible relationships between the independent, mediating, and moderating variables and the outcome variable, we will investigate the antecedents and consequences of any mediating process measured, and test whether the independent variable directly, or indirectly through mediating variables, causes changes in school readiness (Shadish, Cook & Campbell, 2002). Hence causal modelling will allow us to identify the basis for any proportional improvements in outcomes. However, the reliability of both the RCT effect size and the causal modeling will critically depend on 1) power effects and 2) sample size (attrition).

**Estimation of treatment effects:** T-tests from OLS regressions on the continuous outcomes and chi-squared tests from logistic regressions on the binary outcomes will be estimated. Secondly, permutation-based hypothesis testing will be used as an alternative method of assessing the statistical significance of the observed treatment effects. Permutation testing is more suitable than standard bivariate tests, such as t-tests, as it does not depend on distributional assumptions and thus facilitates the estimation of treatment effects in small samples (Ludbrook and Dudley, 1998). A number of simulation studies have found that permutation testing has superior power advantages over parametric t tests, particularly if the data are skewed and the degree of skewness is correlated with the size of the treatment effect (e.g. Hayes, 1996). A permutation test relies on the assumption of exchangeability under the null hypothesis. If the null hypothesis is true, which implies that the programme has no impact, then taking random permutations of the treatment indicator does not change the distribution of outcomes for the high or low treatment group.

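### The second objective asks about the low-treatment supports against the external group (B vs C), but section 12.2 plans only A vs B and a pooled (A+B) vs C

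*Protocol*

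**What the plan says.** Section 4 of the protocol lists two objectives. The first is the randomised comparison of high with low treatment. The second uses a quasi-experimental design and asks whether, "compared to the external comparison group, the low treatment supports leads to improved school readiness skills".

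Section 12.2 fixes two contrasts. One is the randomised pair: "All statistical analysis will involve comparing both treatment group A (high dosage) to treatment group B (low dosage"). The other, in the same sentence, brings in the external community by pooling both programme arms: "groups (A+B) to control group C (external comparison group"). No other section specifies low treatment against the external group.

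Section 7 defines what each group receives:
- High (A): "The high treatment group will receive twice monthly home visits, lasting approximately one hour", plus an invitation to Group Triple P after the 24-month assessment (7.1).
- High and low (A and B): "Both the high and low treatment groups will receive some common supports including developmental materials and book packs" (7.2).
- External (C): "will receive care-as-usual only" (7.3).

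The trial summary gives the sizes as "300 (100 in randomised high treatment group; 100 in randomised low treatment group and 100 in external comparison group").

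**The concern.** One of the two stated objectives has no matching analysis. The contrast that does involve the external group puts the home-visited families into the same arm as the families who received only the low supports, so it estimates a mixture of two treatments.

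The protocol has already chosen the contrast, so this is not a detail left open for the statistical analysis plan. A plan that follows section 12.2 will miss the second objective, and one that follows section 4 will contradict section 12.2. If the pooled result is reported as the answer to the second objective, a programme that works only through home visiting would tend to make the low supports look effective. The better home visiting works, the more often that would happen.

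**Working it through.** **Inputs.** Group sizes are 100, 100 and 100 (sections 1 and 6). Section 12.1 gives 80% power at two-tailed .05 for the randomised pair. It states no numeric effect size: it speaks of small to moderate effects and then of a large one. All effects below are therefore assumptions, in SD units with SD = 1.

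**The plan's own sample size.** It cannot be strictly reproduced without an effect size. By the normal approximation, n per group = 2(1.960 + 0.842)² / d². At d = 0.40 this is 15.70 / 0.16 = 98.1, so 99 per group, and 100 per group gives 80.7% power. So 100 per group fits d of about 0.40. By the same formula d = 0.3 needs 175 per group and d = 0.5 needs 63. The value 0.40 is used below only as one point in a range.

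**What the pooled contrast estimates.** With A and B of equal size,

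(A + B)/2 − C = (B − C) + ½(A − B).

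The first term is the quantity in the second objective. The second is half of the quantity in the first objective. The pooled contrast equals B − C only when A − B is zero, that is, when the null of the primary comparison is true.

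**How often it would mislead.** Suppose the low supports do nothing (B = C), the two communities do not differ and nobody is lost. Let h = A − B. The expected pooled difference is h/2, with

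SE = √(1/200 + 1/100) = √0.015 = 0.1225.

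Two-sided rejection rate = Φ(z − 1.960) + Φ(−z − 1.960), with z = (h/2)/0.1225. One-sided rate = Φ(z − 1.645).

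| Assumed h | Pooled difference | z | Significant, two-sided .05 | Significant, one-sided .05 |
|---|---|---|---|---|
| 0.2 | 0.10 | 0.82 | 12.9% | 20.4% |
| 0.3 | 0.15 | 1.22 | 23.2% | 33.7% |
| 0.4 | 0.20 | 1.63 | 37.2% | 49.5% |
| 0.5 | 0.25 | 2.04 | 53.2% | 65.4% |

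The nominal rate is 5% in both of the last two columns. The one-sided column is shown because section 12.2 reports one-sided p-values for its permutation tests. It does not say which sidedness applies to the contrast with C.

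A simulation of 20,000 trials per row with t-tests gave 13.2%, 22.4%, 36.0% and 50.9% two-sided, slightly below the formula at the larger effects. In the same simulations B vs C rejected in 4.7% to 5.1% of trials, as it should.

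**Precision of B vs C.** SE = √(1/100 + 1/100) = 0.1414. The difference detectable with 80% power at two-sided .05 is 2.802 × 0.1414 = 0.40 SD, against 2.802 × 0.1225 = 0.34 SD for the pooled contrast.

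**The case against.** The strongest reply is that the pooled contrast is a legitimate estimate of something else: taking part in the programme in any form, against usual care. Section 12.2 never says it is the test of the low supports, so the error rates above apply only if someone reads it that way. That is correct, and the conclusion is worded accordingly. But no objective asks about participation in any form, and the objective that is stated still has no analysis. It can also be said that the bracketed sum loosely means each group separately against C. The plus sign favours pooling, and if separate comparisons were meant the sentence still needs correcting.

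A reader might infer several stronger points that the protocol does not support:
- **Permutation tests for the external contrast.** Section 12.2 does say "A permutation test relies on the assumption of exchangeability under the null hypothesis", and exchangeability with a second, non-randomised community is not given by design. But the surrounding text describes permuting only the high and low groups. Using it for C would be an inference from the general sentence about contrasts.
- **No baseline adjustment.** Section 12.2 names regression models, which can take covariates, and promises a detailed analysis plan. An unnamed covariate set is not an error here.
- **B vs C as a test for contamination.** Section 3.2 names contamination as one possible reason for a null result. B vs C mixes contamination with the low supports' own effect and any community difference, so it cannot isolate it. Table 1 schedules direct contamination questions from 6 to 48 months.
- **A rejection rate at a 10% level.** The 0.1 in section 12.2 is the stepdown threshold for a joint null. It is not a one-sided level for a single contrast, and a rate computed at 10% cannot be set against 5%.

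**Conclusion.** The mismatch between sections 4 and 12.2 is real and should be corrected. As written, the plan yields the low-supports effect plus half of the high-versus-low effect, which is the wrong quantity for the second objective. If read as the answer to it, and if the low supports truly do nothing, the chance of a significant result is about 13% to 53% (two-sided .05) for high-versus-low effects of 0.2 to 0.5 SD, against 5%. These rates assume full retention, which the protocol itself does not expect, and no difference between the communities. A community difference would bias any contrast with C, pooled or not.

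A reader might infer that the trial's main result is compromised. It is not: the primary hypothesis in section 3.2 concerns high against low only, and section 12.2 specifies that randomised comparison. The point is confined to the second objective.

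**What to change.** In section 12.2, name B vs C as the analysis of the second objective. Label it quasi-experimental, as section 4 already does, and adjust it for baseline variables collected in all three groups (section 10.4 provides for data collection from all three within the same period). The choice of covariates and method can stay with the statistical analysis plan. If (A+B) vs C or A vs C is still wanted, keep it as an additional contrast under its own label: participation in any form, or the full programme, against usual care.

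The cost is a sentence or two of text and no new data. Statistically, the unadjusted standard error at full retention rises from about 0.122 to 0.141 SD, and the detectable difference from about 0.34 to 0.40 SD.

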**6. STUDY Design**

The study is a two-arm researcher-blind, randomised controlled trial (RCT), to test the effectiveness of the PFL home visiting programme and group Triple P for pregnant women from socioeconomically disadvantaged communities. The trial will involve 300 families in total. 200 will be randomly allocated into one of two groups:

(1) **High treatment group**, who will receive the PFL intervention (described below) (n=100)

(2) **Low treatment group** (n=100)

A third external comparison group will also be recruited from another similar community

(3) **External comparison group** (n=100).

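### Section 12.2 gives one set of methods for both contrasts and states no control for community differences in the non-randomised comparison with group C

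*Protocol*

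**What the plan says.** **Source of group C.** Protocol section 6: "A third external comparison group will also be recruited from another similar community". Section 7.3 repeats that this group is one "which will be selected from a socio-demographically similar community, will receive care-as-usual only". Similarity is claimed for the community; no matching of families is described. Section 9.1 makes residence in the PFL catchment an inclusion criterion, and non-residence is an exclusion.

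**Objective.** The second bullet of section 4 reads: "To use a quasi-experimental design to evaluate whether, compared to the external comparison group, the low treatment supports leads to improved school readiness skills". The contrast there is low treatment (B) vs C.

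**Contrasts in the analysis.** Section 12.2: "All statistical analysis will involve comparing both treatment group A (high dosage) to treatment group B (low dosage), and groups (A+B) to control group C". The contrast there pools A and B against C.

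**Methods.** Section 12.2 continues: "T-tests from OLS regressions on the continuous outcomes and chi-squared tests from logistic regressions on the binary outcomes will be estimated". Permutation tests follow, with 100,000 replications and one-sided p-values, and then a stepdown adjustment built on the same permutations with a threshold of p < 0.1. On the basis for permutation it says: "A permutation test relies on the assumption of exchangeability under the null hypothesis". The sentences that explain this, and the definition of the test statistic, speak of the high and low treatment groups.

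**Use of baseline data.** Inverse probability weighting is specified, with a model for completing an interview at each assessment point. No model for membership of group C is mentioned.

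**The concern.** In A vs B, random allocation makes the group labels exchangeable if the programme does nothing. In a contrast with C, the absence of a programme effect does not imply equal outcome distributions, because every C family lives elsewhere. There is also a possible selection difference: trial families must accept assignment to either intervention group, while C families face no allocation.

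The second objective rests wholly on C. If section 12.2 is applied to that contrast with nothing added, a small p-value says that the groups differ. It does not say whether the supports or the community made them differ. The usual safeguard of a baseline measure of the outcome is unavailable, since section 10.4 notes that a pre-test of the child is not possible. Family-level baseline covariates are therefore the main tool, and section 12.2 does not assign them this task.

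The contrast itself is also unsettled. The pooled comparison averages the effect of the full programme with that of the low-treatment supports, so it does not answer the question in section 4, which is about the low-treatment supports alone.

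**Working it through.** **The plan's own figures.** Section 12.1 states 80% power at two-tailed 0.05 for the 200 randomised families, with no numerical effect size. It gives no power or sample size for a contrast with C, so there is no figure to reproduce for this point. As a yardstick, 100 per group gives 80% power for (1.960 + 0.842) × √(2/100) = 0.396 SD.

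**Inputs.** Planned sizes from sections 6 and 12.1: A = 100, B = 100, C = 100. Outcome SD set to 1. Programme effect set to 0. The community difference δ, in SD units and positive when it favours the PFL area, is an assumption; the protocol gives no value.

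**Standard errors.**
- (A+B) vs C: √(1/200 + 1/100) = 0.122
- B vs C: √(1/100 + 1/100) = 0.141

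**Rejection rates.** One-sided: 1 − Φ(z₁₋α − δ/SE). Two-sided 5%: 1 − Φ(1.960 − δ/SE) + Φ(−1.960 − δ/SE).

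Example, (A+B) vs C with δ = 0.1: δ/SE = 0.1/0.1225 = 0.816, and 1 − Φ(1.645 − 0.816) = 0.204.

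| Contrast | δ (SD) | One-sided 5% | One-sided 10% | Two-sided 5% |
|---|---|---|---|---|
| (A+B) vs C | 0 | 5.0% | 10.0% | 5.0% |
| (A+B) vs C | 0.1 | 20.4% | 32.1% | 12.9% |
| (A+B) vs C | 0.2 | 49.5% | 63.7% | 37.2% |
| (A+B) vs C | 0.3 | 78.9% | 87.9% | 68.8% |
| B vs C | 0.1 | 17.4% | 28.3% | 10.9% |
| B vs C | 0.2 | 40.9% | 55.3% | 29.3% |
| B vs C | 0.3 | 68.3% | 79.9% | 56.4% |

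The one-sided columns correspond to the p-values that section 12.2 says it will report. The 10% column uses the stepdown threshold for a single outcome; it is not a calculation of the joint stepdown.

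**Does permutation protect?** A simulated one-sided permutation test of (A+B) vs C (1,500 data sets, 999 permutations each, normal outcomes) rejected at 5% in 5.4%, 20.1%, 49.8% and 77.3% of data sets for δ = 0, 0.1, 0.2 and 0.3. These agree with the formula, so permutation gives no protection against a community difference.

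**The opposite direction.** Suppose the programme truly adds 0.2 SD and the PFL area starts 0.2 SD behind. The net difference is 0.2 − 0.2 = 0, and the one-sided 5% test rejects 5.0% of the time instead of 49.5%.

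**The case against.** Several points on the other side are sound.

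- **Permutation is written for high vs low.** A reader might infer that the protocol plans to shuffle labels across all three groups. It does not say so: the exchangeability argument and the test statistic name only the high and low groups. Its use with C follows only from the sentence that extends all analysis to both contrasts.
- **The models are not called unadjusted.** Covariates are neither named nor excluded in the OLS and logistic regressions. What can be said is that no adjustment for community differences is stated.
- **No text says that community differences will be reported as programme effects.** Section 4 labels the comparison quasi-experimental, section 3.2 frames the primary hypothesis as high vs low, and section 12.2 ties its causal statement to the randomised experiment. Misattribution is a risk, not a declared plan.
- **A statistical analysis plan is promised and is not at hand.** Covariate lists and balance tables are commonly left to it, and their absence alone would be no finding. This answers only part of the point. Section 12.2 itself fixes the contrasts, tests, replications, weighting and stepdown, and says they cover all analysis. A later plan that treated C differently would have to depart from that wording.
- **The size and direction of δ are hypothetical.** Under one-sided testing, a difference favouring C lowers the false-positive rate. That is correct, but it trades a false claim for a hidden benefit.
- **Adjustment cannot remove all of the confounding.** With one comparison community, measured family characteristics account for only part of any community effect. This limits what the fix can achieve and is a reason to label the contrast plainly.

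**Conclusion.** The point holds in this form: section 12.2 applies one set of methods to a randomised and a non-randomised contrast, its justification by exchangeability is secured only for the randomised one, and it states no control for baseline differences between communities. The stronger readings, that the protocol commits to unadjusted permutation across all three groups or to crediting the programme with community differences, go beyond the text.

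With no programme effect, an assumed difference of 0.1 or 0.2 SD in favour of the PFL area raises the rejection rate for (A+B) vs C from 5% to about 20% or 50% one-sided (13% or 37% two-sided). A difference of 0.2 SD is about half the 0.40 SD that 100 per group can detect with 80% power. The figures assume full planned numbers, no attrition, continuous outcomes and no effective adjustment; with fewer families the inflation would be smaller. They illustrate sensitivity and do not estimate the actual bias.

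The randomised primary comparison is unaffected. The second objective depends entirely on C, so this should be corrected. The mismatch between B vs C in section 4 and (A+B) vs C in section 12.2 needs settling in any case.

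**What to change.** In section 12.2:

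1. State that permutation and stepdown inference applies to the randomised high-low contrast only.
2. For any contrast with C, adjust for baseline variables that Table 1 already lists, such as maternal age, education, employment and income, number of children, material deprivation and week of pregnancy. Inverse-probability-of-group weighting, regression, or both would serve. Keep these weights distinct from the attrition weights, and say how the two are combined.
3. Report baseline balance and overlap before and after adjustment.
4. Describe the result as non-randomised supporting evidence in which residual community confounding is possible.
5. Reconcile sections 4 and 12.2 on whether the contrast is low treatment vs C or A+B vs C. If both are wanted, say which one addresses the second objective.

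The cost is about a paragraph of text and modest extra analysis. Section 10.4 plans data collection in all three groups over the same period, so no new data are needed. Intervals for the group C contrast may be wider, more so if the communities overlap poorly on the baseline variables.
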